## 8.3 Adverse Events and Serious Adverse Events

### 8.3.1 Definition of Adverse Events (AE)

An Adverse Event (AE) is any unfavorable and unintended sign (including an abnormal laboratory finding), symptom, or disease temporally associated with the use of a medical treatment or procedure that may or may not be considered related to the medical treatment or procedure. An AE is a term that is a unique representation of a specific event used for medical documentation and scientific analyses.

All subjects will be monitored for AEs during the study. Assessments will be made by monitoring the following parameters: the subject’s clinical symptoms, laboratory, pathological, radiological or surgical findings, physical examination findings, or findings from other tests and/or procedures.

Any worsening (i.e., any clinically significant adverse change in the frequency or intensity of a preexisting condition) should be considered an AE. A diagnosis or syndrome should be recorded in the electronic case report forms (eCRFs) rather than the individual signs or symptoms of the diagnosis or syndrome.

Abuse, withdrawal, sensitivity or toxicity to dronabinol should be reported as an AE. Overdose, accidental or intentional, whether or not it is associated with an AE should be reported. Any sequela of an accidental or intentional overdose of study agent should be reported as an AE on the AE eCRF. If the sequela of an overdose is an SAE, then the sequela must be reported on an SAE report form and on the AE eCRF. The overdose resulting in the SAE should be identified as the cause of the event on the SAE report form and eCRF but should not be reported as an SAE itself.

All AEs will be recorded by study personnel from the time the subject signs informed consent until 28 days after the last dose of dronabinol/placebo or until the final visit, whichever is longer, as well as those SAEs made known to the investigator at any time thereafter that are suspected of being related to study agent. Adverse events and SAEs will be recorded on the AE page of the eCRF.

Though dronabinol is an FDA approved medication with a known safety profile surveillance will occur for both known and unknown adverse events.

All laboratory abnormalities will be evaluated by the investigator or a qualified designee and recorded in the eCRF.

Regardless of severity grade, only laboratory abnormalities that fulfill a seriousness criterion need to be documented as a SAE.

If a laboratory abnormality is one component of a diagnosis or syndrome, then only the diagnosis or syndrome should be recorded on the AE page/screen of the eCRF. If the abnormality was not a part of a diagnosis or syndrome, then the laboratory abnormality should be recorded as the AE. If possible, the laboratory abnormality should be recorded as a medical term and not simply as an abnormal laboratory result (e.g., record thrombocytopenia rather than decreased platelets).

### 8.3.2 Definition of Serious Adverse Events (SAE)

An adverse event (AE) or suspected adverse reaction is considered "serious" if, in the view of the investigator, it results in any of the following outcomes:

- Results in death
- Is life-threatening (i.e., in the opinion of the investigator, the subject is at immediate risk of death from the AE)
- Requires inpatient hospitalization or prolongation of existing hospitalization (hospitalization is defined as an inpatient admission, regardless of length of stay)
- Results in persistent or significant disability/incapacity (a substantial disruption of the subject’s ability to conduct normal life functions)
- Is a congenital anomaly/birth defect
- Constitutes an important medical Important medical events are defined as those occurrences that may not be immediately life threatening or result in death, hospitalization, or disability, but may jeopardize the subject or require medical or surgical intervention to prevent one of the other outcomes listed above. Medical and scientific judgment should be exercised in deciding whether such an AE should be considered serious.

For this study, events not considered to be SAEs are hospitalizations for:

- Routine treatment or monitoring not associated with any deterioration in condition.
- The administration of blood or platelet transfusion as routine treatment of studied
- Emergency outpatient treatment or observation that does not result in admission, unless fulfilling other seriousness criteria
- Hospitalization for treatment of uncomplicated sickle cell pain crisis as defined by the investigator

If an AE is considered serious, both the AE eCRF and the SAE Report Form must be completed. For each SAE, the investigator will provide information on severity, start and stop dates, relationship to study agent, action taken regarding study agent, and outcome.

The principal investigator is responsible for reporting SAEs to the IRB and other applicable regulatory authority. The principal investigator is responsible for submitting follow-up reports for all SAEs regarding the patient’s subsequent course until the SAE has resolved or until the patient’s condition stabilizes (in the case of persistent impairment), or the death of the patient.

### 8.3.3 Classification of an Adverse Event

#### 8.3.3.1 Severity of Event

The severity of AEs will be graded and reported using the NCI Common Terminology Criteria for Adverse Events (CTCAE) v5.0. The full text of the NCI CTCAE is available online at: https://evs.nci.nih.gov/ftp1/CTCAE/CTCAE_5.0/

For adverse events (AEs) not included in the protocol defined grading system, the following guidelines will be used to describe severity.

- Grade 1: Mild – Events require minimal or no treatment and do not interfere with the participant’s daily
- Grade 2: Moderate – Events result in a low level of inconvenience or concern with the therapeutic measures. Moderate events may cause some interference with
- Grade 3: Severe – Events interrupt a participant’s usual daily activity and may require systemic drug therapy or other Severe events are usually potentially life- threatening or incapacitating. Of note, the term “severe” does not necessarily equate to “serious”.
- Grade 4: Life-threatening - Events resulting in a potential threat to life; urgent intervention extreme limitation in activity, significant assistance required; significant medical intervention/therapy required, hospitalization or hospice care probable
- Grade 5: Fatal - Event results in death related to AE

The distinction between the seriousness and the severity of an AE should be noted. Severity is a measure of intensity; thus, a severe reaction is not necessarily a serious reaction. For example, a headache may be severe in intensity, but would not be classified as serious unless it met one of the criteria for serious events

#### 8.3.3.2 Relationship to Study Intervention

All adverse events (AEs) must have their relationship to study intervention assessed by the clinician who examines and evaluates the participant based on temporal relationship and his/her clinical judgment. The degree of certainty about causality will be graded using the categories below. In a clinical trial, the study product must always be suspect.

- Definitely Related – There is clear evidence to suggest a causal relationship, and other possible contributing factors can be ruled The clinical event, including an abnormal laboratory test result, occurs in a plausible time relationship to study intervention administration and cannot be explained by concurrent disease or other drugs or chemicals. The response to withdrawal of the study intervention (de-challenge) should be clinically plausible. The event must be pharmacologically or phenomenologically definitive, with use of a satisfactory re-challenge procedure if necessary.
- Probably Related – There is evidence to suggest a causal relationship, and the influence of other factors is The clinical event, including an abnormal laboratory test result, occurs within a reasonable time after administration of the study intervention, is unlikely to be attributed to concurrent disease or other drugs or chemicals, and follows a clinically reasonable response on withdrawal (de-challenge). Re-challenge information is not required to fulfill this definition.
- Potentially Related – There is some evidence to suggest a causal relationship (e.g., the event occurred within a reasonable time after administration of the trial medication). However, other factors may have contributed to the event (e.g., the participant’s clinical condition, other concomitant events). Although an AE may rate only as “possibly related” soon after discovery, it can be flagged as requiring more information and later be upgraded to “probably related” or “definitely related”, as
- Unlikely to be related – A clinical event, including an abnormal laboratory test result, whose temporal relationship to study intervention administration makes a causal relationship improbable (e.g., the event did not occur within a reasonable time after administration of the study intervention) and in which other drugs or chemicals or underlying disease provides plausible explanations (e.g., the participant’s clinical condition, other concomitant treatments).
- Not Related – The AE is completely independent of study intervention administration, and/or evidence exists that the event is definitely related to another There must be an alternative, definitive etiology documented by the clinician.

Causality should be assessed and provided for every AE/SAE based on currently approved drug label. Causality is to be reassessed and provided as additional information becomes available.

#### 8.3.3.3 Expectedness

The PI or Sub-Investigator will be responsible for determining whether an adverse event (AE) is expected or unexpected. An AE will be considered unexpected if the nature, severity, or frequency of the event is not consistent with the risk information previously described for the study intervention and in the currently approved drug label.

### 8.3.4 Time Period and Frequency for Event Assessment and Follow-Up

All AEs will be recorded by study personnel from the time the subject signs informed consent until 28 days after the last dose of dronabinol/placebo or until the final visit, whichever is longer, as well as those SAEs made known to the investigator at any time thereafter that are suspected of being related to study agent.

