| **Study Population:** | - Age >18 years - Clinical diagnosis of SCD (HbSS, HbSC, HbSβ+; Thal, HbSβ0Thal, HbS variants) - Baseline score of 60 or lower on the ASCQ-Me 7-day pain interference domain - If on a SCD modifying therapy (hydroxyurea, regular blood transfusions, L-glutamine, voxelotor, crizanlizumab), on stable dose for at least 3 months - If using opioids for pain at home, on stable dose for at least 3 months - One urine toxicology negative for cannabinoids within 30 days of randomization - No known intolerance to dronabinol, or marijuana - No history of psychotic episode, psychosis, or active suicidality - No contraindication to dronabinol with attention to potential side effects, concurrent medications/substances, and concurrent medical problems, as evaluated by a physician - Willing to abstain from cannabis, medical and illicit, during study weeks 1 through 8 - Not pregnant or nursing - If a woman capable of becoming pregnant, willing to use a medically accepted form of birth control for the duration of study participation.  Accepted forms include oral contraception, medroxyprogesterone, contraceptive implants or patch, surgical sterilization, total abstinence. - Able to consent for research - Daily cannabis use - Diagnosis of active substance use disorder |
| **Phase:** | 2 |
| **Description of Sites/Facilities Enrolling Participants:** |  |
| **Description of Study Intervention:** | Dronabinol or matching placebo |
| **Study Duration:** | 48 months |
| **Participant Duration:** | 8 weeks |

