Because this project focuses on a controlled substance, confidentiality is a major concern. We will be collecting personal information from participants to facilitate follow up and will be asking questions about sensitive data including illicit drug use, alcohol use, mental health, and health status. Our procedures to maintain confidentiality are addressed below.

Risks related to dronabinol use:

Dronabinol is an FDA approved medication with a known safety profile.  Anticipated side effects are listed here.  Most Common Side Effects include: Dizziness, Euphoria, Paranoid Reaction, Sleepiness, Abnormal thoughts, Abdominal pain, Nausea, Vomiting. Serious Side Effects include: Worsening mental (psychiatric) symptoms. Psychiatric symptoms can worsen in people who have mania, depression, or schizophrenia and who take dronabinol. Dronabinol taken with medicines that cause psychiatric symptoms can worsen psychiatric symptoms. Elderly people who take dronabinol may have a greater risk of having psychiatric symptoms. Problems thinking clearly.  Trouble remembering things, concentrating, have increased sleepiness, or confusion. Elderly people may have a greater risk of having problems thinking clearly. Changes in blood pressure. Dronabinol may increase or decrease blood pressure, especially when patients start taking dronabinol or when the dose is changed. Elderly people, especially those with dementia, and people with heart problems may have an increased risk of changes in blood pressure and an increased risk of falls.

Physical Dependence: is a condition that develops as a result of the body adapting to the response of the drug due to its repeated use. The symptoms of physical dependence show at a certain dose when the continuation of drug use is discontinued in an abrupt/sudden manner or when the drug dose is reduced significantly. This effect has only been evidenced by the termination of drug administration. Physical dependence can develop during chronic therapy with dronabinol capsules and can also develop after chronic abuse of marijuana.

Hazardous Activities

Dronabinol capsules can cause and may impair the mental and/or physical abilities required for the performance of hazardous tasks such as driving a motor vehicle or operating machinery. You should not operate motor vehicles or other dangerous machinery until you are certain that this study medication does not affect you adversely.

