## 4.2 Scientific Rationale for Study Design

People with sickle cell disease (SCD) have chronic pain from multiple sources^2,3,15^ Inflammation is a driver of pain, end organ damage and early mortality in SCD.^16^ Tetrahydrocannabinol (THC) is a partial agonist for cannabinoid receptors (CB1 and CB2), and has been shown to be effective for the treatment of chronic pain and neuropathic pain in conditions such as cancer and multiple sclerosis.^6,17,18^ There is also evidence from murine models of SCD that CB1 agonists can reduce signs of chronic and neuropathic pain as well as inflammatory cytokines that are important in pain development in SCD.^3,4,19^ The proposed research is built on the scientific premise that dronabinol, an FDA-approved synthetic THC medication may treat chronic pain in SCD and reduce inflammation, and therefore is a promising agent for either the treatment of chronic pain or for treatment of the disease directly through reduction of inflammation.

Randomization will be done 1:1 to dronabinol or placebo in blocks of four, stratified by pain type (neuropathic or not) and past-year cannabinoid use (yes or no). Randomization will be done by the pharmacy. Neuropathic pain will be defined by LANSS score >12. Past-year cannabis use will be defined by self-report of any cannabinoid use (medical, illicit, or cannabidiol containing (CBD) products) in the past year. Based on our prior experience as well as the experience of others, we expect 50% to have neuropathic pain and 50% to have past-year cannabis use after excluding frequent cannabis users.^9,40,61^

The treatment duration will be 8 weeks. Studies of cannabis for the improvement of neuropathic pain in other diseases have ranged in duration from 2 to 26 weeks. Another important component of chronic pain in SCD is chronic inflammation. Changes in inflammatory markers can also take weeks to occur, in studies of acute infections markers of inflammation such as CRP can take up to 6 weeks to normalize.62 Therefore, a study aimed at improving chronic pain in SCD or reducing inflammation should be done over weeks to months. We have chosen 8 weeks which we expect will be long enough to detect efficacy in pain and inflammatory outcomes and identify adverse effects.

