## 4.4 End of Study Definition

A participant is considered to have completed the study if he or she has completed all phases of the study including the last visit or the last scheduled procedure shown in the Schedule of Activities (SoA), Section 1.3

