## 8.2 Safety and Other Assessments

We have well-established protocols to screen for medical and psychiatric eligibility. [name] conduct a thorough medical and psychiatric screening of potential participants who meet initial screening criteria and who provide informed consent. Eligibility criteria are detailed in Human Subjects and the determination of eligibility will include:

- Second screening visit. At the screening visit with [name] potential participants will be further assessed for medical and psychiatric eligibility. A physical examination will be performed, women with reproductive potential will take a pregnancy test, and psychiatric disease and substance use disorders will be assessed using the following standardized instruments: 1) the Prodromal Questionaire -Brief (PD-B) a short structured interview to assess for psychotic symptoms; and 2) the Columbia Suicide Severity Rating Scale (CSSR).

Throughout the proposed study, [name] will be responsible for continual medical oversight of patients. All participants will be given oral and written instructions about management of adverse medication effects and emergency contact information prior to initiating medication therapy.

Adverse events, including cardiovascular events, will be assessed at weeks 2, 4, 6, and 8 by asking participants about symptoms that emerged or worsened since the start of medication treatment, whether or not they were thought to be related to study medication. Participants will be asked about treatment-emergent symptoms using both a structured interview and open-ended questions. In the structured interview, we will assess for the presence of specific symptoms reported among ≥ 5 % of participants receiving dronabinol in published research, including (but not limited to) nausea, headache, anxiety, dizziness, paranoid thoughts, sleepiness, euphoria. We chose the threshold of 5% as the majority of published dronabinol studies did not report symptoms that occurred in <5% of participants. Treatment emergent psychiatric symptoms will be further assessed using structured psychometric instruments at each research visit (as described below). All documented adverse events will be documented in case report forms and followed up to resolution or end of study.

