### 8.3.5 Adverse Event Reporting

The reporting of AEs and SAEs will start when the patient signs the informed consent for the study throughout the treatment period and up to and including the 28-day follow-up period. All new AEs occurring during that period must be recorded (if SAEs, they must be reported to the Data Safety Monitoring Committee (DSMC) and IRB as per institutional guidelines). AEs will be recorded per SOPs.

The investigator will report the action taken with study agent as a result of an AE or SAE, as applicable (e.g., discontinuation, interruption, or dose reduction of study agent, as appropriate) and report if concomitant and/or additional treatments were given for the event.

- Patients receiving treatment with dronabinol capsules should be alerted to the potential for additive central nervous system depression if dronabinol capsules is used concomitantly with alcohol or other CNS depressants such as benzodiazepines and barbiturates.

Study agent will be discontinued for all AEs grade 3 or above. Study agent will not restarted until AE has resolved to grade 1 for all objective events or until patient grade 1 or grade 2 and patient requests to restart drug despite symptoms for all subjective events. This is because some adverse events of dronabinol may be seen as a benefit by patients, for example dronabinol may cause tiredness but some patients with SCD complain of insomnia.

Study agent will not be discontinued for expected AEs or SAEs determined to not be due to dronabinol such as a pain crisis.

For patient reported AEs grade 1 or 2 the patient and investigator will decide together whether to discontinue study agent, lower the dose of study agent, or to continue on full dose if the patient feels that the benefit of study agent outweighs the discomfort of the AE of the AE is in fact perceived as a benefit (i.e. sleepiness may be a benefit if the subject previously suffered from poor sleep).

The investigator will report the outcome of the event for both AEs and SAEs. All SAEs that have not resolved upon discontinuation of the subject’s participation in the study must be followed until recovered (returned to baseline), recovered with sequelae, or death (due to the SAE)

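### All adverse events are to be recorded until 28 days after the last dose, but no contact is scheduled after week 8 to elicit them in participants treated to the end

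*Protocol*

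**What the plan says.** **The recording window.** Sections 8.3.1 and 8.3.4 start AE recording at consent and continue it "until 28 days after the last dose of dronabinol/placebo or until the final visit, whichever is longer". Section 8.3.5 describes the same window as a phase of the study, with reporting "throughout the treatment period and up to and including the 28-day follow-up period", and adds that "All new AEs occurring during that period must be recorded". Section 8.3.1 lists withdrawal from dronabinol among the events to be reported as AEs.

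**The schedule.** The AE row of the schedule of activities (section 1.3) has entries at baseline and weeks 2, 4, 6 and 8, and the table has no later column. Section 8.2 agrees: "Adverse events, including cardiovascular events, will be assessed at weeks 2, 4, 6, and 8", by structured interview and open questions. It follows documented AEs to resolution or the end of the study. Section 4.2 states "The treatment duration will be 8 weeks", and the synopsis gives 8 weeks as the participant duration. Section 4.4 counts a participant as complete after all phases, "including the last visit or the last scheduled procedure shown in the Schedule of Activities (SoA), Section 1.3".

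**The named risk.** Section 2.3.1 lists physical dependence, with symptoms when dosing stops suddenly or the dose is cut significantly. It says of dependence: "This effect has only been evidenced by the termination of drug administration".

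**The concern.** The protocol requires the recording of all new events in a period for which it schedules no contact. In a participant who takes drug to week 8, the last scheduled questioning coincides with the last dose, so the post-dose part of the window begins just as elicitation ends.

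Safety and tolerability are a stated secondary objective. The protocol anticipates withdrawal symptoms, and in participants treated to week 8 symptoms from stopping would first appear after the last visit. Sites could not reliably meet sections 8.3.4 and 8.3.5 by following the schedule. A small number of post-treatment events might reflect only that nobody asked. Participants who stop drug early are asked in section 7.1 to keep attending visits, so they are questioned while off drug. Those who finish treatment are not.

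**Working it through.** This is calendar arithmetic. No sample-size or power figure enters it.

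**Inputs**
- First dose taken as day 0, and week 8 as day 56 (sections 1.3 and 4.2).
- Last scheduled contact: day 56 (sections 1.3 and 8.2).
- Post-dose window: 28 days (sections 8.3.1, 8.3.4 and 8.3.5).
- The window opens at consent (sections 8.3.1 and 8.3.4). Screening must finish within 30 days of consent (section 8.1). I assume dosing starts when screening ends, because the protocol gives no interval between the two.

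**1. Participant treated to week 8**
- Required end of window = last dose + 28 = 56 + 28 = day 84 (week 12).
- The rule takes the later of this date and the final visit. Day 84 is later than day 56, so day 84 applies.
- Days without a scheduled contact = 84 − 56 = 28, which is all 28 post-dose days.

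**2. Share of the whole AE window**
- Screening of 0 days: 28 / 84 = 33%.
- Screening of 30 days: 28 / (84 + 30) = 28 / 114 = 25%.

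**3. Participants who stop earlier**

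Post-dose days inside the schedule = 56 − day of last dose, up to a maximum of 28, provided the participant keeps attending.

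| Last dose (day) | Inside the schedule | Outside the schedule |
| --- | --- | --- |
| 28 or earlier | 28 | 0 |
| 42 | 14 | 14 |
| 56 | 0 | 28 |

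The latest last-dose day with full coverage is 56 − 28 = day 28. The gap therefore also touches anyone who stops between days 29 and 55.

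**4. Alternative reading of treatment length**

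Section 4.1 can be read as one week of titration followed by 8 further weeks. The last dose would then be day 63 and the window would end at 63 + 28 = day 91 (week 13). The unscheduled stretch after day 56 would be 91 − 56 = 35 days: 7 on drug and 28 off. The share would be 35 / 91 = 38% with no screening time and 35 / 121 = 29% with 30 days of it. I use the 8-week reading in the conclusion because section 4.2 and the synopsis support it.

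**5. Whether another provision fills the gap**
- Section 7.2 encourages further follow-up of participants already experiencing drug-related AEs, if feasible.
- Sections 7.1 and 8.3.5 follow serious adverse events (SAEs) already identified.
- Section 8.3.4 accepts suspected-related SAEs that become known to the investigator at any later time.
- Section 8.3.5 refers AE recording to standard operating procedures that are not shown. As worded, this concerns recording and schedules no contact.

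None of these provides for finding a new, non-serious AE in a participant who has completed treatment.

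**The case against.** The strongest reply is that recording an event differs from scheduling a question about it, and that contact after week 8 is not excluded. Participants receive written instructions and emergency contact details (section 8.2), most are patients of the recruiting centre (section 5.5), and the routes in step 5 remain open. This stands to a point. A reader might infer that nobody can be reached after week 8 and that every later event is lost. The protocol does not support that. Volunteered events, ongoing related AEs and known SAEs could still be captured. What is missing is systematic elicitation of new non-serious events.

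Four other inferences also go too far.
- **That 56 of the planned 70 participants would have none of their 28 days observed.** The 20% in section 9.2 is attrition from the study. The protocol gives no rate of stopping drug, and some who complete the visits may have stopped drug earlier, so this number cannot be derived.
- **That a planned estimate is biased low.** Section 9.4.4 compares the number and percentage of participants with new AEs by arm, using Fisher's exact test. It plans no post-dose rate and no comparison of early stoppers with completers. The visit schedule is the same in both arms.
- **That dependence is wholly unobserved.** Section 2.3.1 also ties its symptoms to significant dose reduction. Reductions during treatment are allowed and fall under the questioning at weeks 2 to 8. The section links dependence to chronic therapy and does not say whether 8 weeks qualifies.
- **That the uncovered share is simply one third.** That is the upper end on the 8-week reading, because the window opens at consent.

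**Conclusion.** The inconsistency is real and should be corrected before the safety data are relied on. The AE window runs to 28 days after the last dose, while every scheduled contact ends at week 8. For a participant treated to week 8, 28 of 28 post-dose days have no scheduled contact, about 25% to 33% of the full AE window. This assumes 8 weeks of treatment, 0 to 30 days of screening, and dosing that starts when screening ends.

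The consequence is confined to safety. New non-serious AEs after treatment, withdrawal symptoms among them, may be under-ascertained in those with the longest exposure, and a low count would carry little information. The primary endpoint, measured from baseline to week 8, is unaffected. How many events would be missed cannot be estimated from the protocol.

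**What to change.** Reconcile sections 8.3.1, 8.3.4 and 8.3.5 with sections 1.1, 1.3, 4.4 and 8.2 in one of two ways.

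1. **Keep the window and schedule a contact.** Add one telephone or telemedicine AE contact at 28 days after the last dose to the schedule of activities and section 8.2, using the same questions as at the other visits and asking about withdrawal symptoms. Extend the participant duration and the completion definition to include it. Section 8.1 already allows telemedicine for the week 2 and week 6 safety assessments. The cost is one call per participant and matching wording in participant materials. A single call asks participants to recall 28 days, twice the two-week interval used during treatment.
2. **Keep the schedule and restate the window.** End routine AE recording where the schedule ends, and say plainly that post-treatment and withdrawal events are not systematically ascertained. This costs only wording, but gives up information on a risk that the protocol names.

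The first option serves the secondary safety objective better. Under either option, state whether treatment lasts 8 or 9 weeks, so that the date of the last dose, and with it the end of the window, is unambiguous.
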